### Objectives and endpoints

The primary objective of this study is to determine the effectiveness of home-based contact management, including TPT initiation and follow-up, using community-based healthcare workers to increase TPT initiation as compared to facility-based contact management. The primary endpoint is the cluster-level ratio of the number of household child contacts less than 15 years of age in Ethiopia and less than 5 years of age in South Africa initiated on TPT (3HP, 3RH, or 6H) per index patient, comparing the intervention to the control arm (Table 1). Because we anticipate heterogeneity in the epidemiology of TB and potential differences in the response to the intervention between countries, the primary outcome will be assessed across countries and within countries.

**Table 1 Tab1:** Primary and secondary outcomes for the CHIP-TB trial

**Primary outcome**	**Outcome description**	
TPT initiation among child contacts	The cluster-level ratio of the number of household child contacts less than 15 years of age in Ethiopia and less than 5 years of age in South Africa initiated on TPT per index patient, comparing the intervention to the control arm	
**Secondary outcome**	**Outcome description**	
Child contact identification	The cluster-level ratio of the number of household child contacts less than 15 years of age in Ethiopia and less than 5 years of age in South Africa identified per index patient	
Continuum of care	The cluster-level proportions of estimated child contacts who progress through each stage of the pediatric TB prevention continuum of care (identification, screening, initiation, and completion) overall and by age, by TPT regimen, and by country. *estimated child contacts will be calculated using DHS data	
Treatment completion (as defined by WHO TPT Handbook)	• Proportion of children initiated on TPT who successfully completed TPT • Proportion of children initiated on TPT who were lost to follow-up • Proportion of children initiated on TPT with incident TB (treatment failure) • Proportion of children initiated on TPT who died • Proportion of children initiated on TPT who discontinued TPT due to: toxicity, drug-drug interaction, severe illness (e.g., malaria), pregnancy, or family preference *Treatment completion was defined as 11 doses in 16 weeks for 3HP and 68 doses in 4 months for 3RH [19].	
**Implementation outcome**	**Quantitative assessment**	**Qualitative assessment**

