### Study description and procedures

#### Intervention arm

In the intervention arm, child TB contact management, including contact tracing, child evaluation, and TPT initiation and follow-up, will take place in the community at the child’s home (Fig. 2). Newly diagnosed eligible TB index patients will be asked to give consent to a home visit. The initial home visit will include TB symptom screening for all TPT-eligible children (< 15 years in Ethiopia and < 5 years in South Africa), and either TPT initiation for asymptomatic child contacts or clinic referral for all symptomatic child contacts. TB screening and TPT initiation will be conducted by either a research nurse (South Africa) or health extension worker (Ethiopia) in the home. Children who screen negative (0 of 8 symptoms present, see the “ TB screening and evaluation” section) will be initiated on TPT. Children who screen positive (any one symptom is present) will be counseled and referred to the local clinic for evaluation as per the local standard of care. The community health team (in Ethiopia) or the research nurse (in South Africa) will revisit the household monthly for three months to ensure linkage to care.

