#### Treatment follow-up and adherence

Children initiated on TPT will be followed at home (intervention) or in clinic (control) monthly for the duration of TPT. Adherence will be measured by return visits and pill counts in both groups. Children will also be re-screened for TB symptoms during each follow-up visit.

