### Statistical analysis

#### Primary and secondary outcome analyses

Summary statistics of the enrolled index patients will be presented stratified by arm and study site. Analysis of the primary outcome of the number of child contacts less than of 15 years of age in Ethiopia and less than 5 years of age in South Africa who initiate TPT per index patient diagnosed will be stratified by country. Cluster-level ratios will be compared between arms using an unpaired t-test which has been shown to be robust for a relatively small number of clusters [24]. The ratio of the study arm mean ratios and the corresponding 95% confidence interval will be calculated. A log-transformation of the cluster-level ratios will be applied before applying the *t*-test if the outcomes are highly skewed. If the number of index patients varies substantially between clinics, weighted (by clinic size) mean ratios will be used. If the sample size allows, we will compare the numbers of children started on TPT between arms stratified by TPT regimen (3HP vs 3RH) and children’s age groups (^3^5 vs <5 for Ethiopia).

Secondary outcomes to be compared between arms will be the number of child contacts identified (using index patient’s clinic-based contact tracing report, the child contact management file, and the community-level file maintained by the community health team) per index patient, and the proportions of these who are screened, initiated on TPT and who complete TPT. As done for the primary outcome, cluster-level summaries for secondary outcomes will also be compared between arms. Count outcomes will be compared using Poisson regression, and cluster-level proportions (after a log-transformation, if necessary) will be compared using a *t*-test.

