We will provide summary statistics of TPT completion rates and losses to follow-up discontinuation (due to incident TB, side effects, transfer out, other reasons, or death) stratified by study arm and site. TPT completion will be defined as three monthly follow-up visits over a 4-month period (3HP or 3HR) or six monthly visits over a 9-month period (6H). Loss to follow-up will be defined as no return visit within three months of the child’s last recorded visit. Other reported outcomes will include new HIV diagnoses among children who are referred for ART initiation. All outcomes will be summarized by the study arm, and formal statistical tests will be conducted if the number of events observed allows. All data will be abstracted by study staff from index patient and child contact management files.

Acceptability of the intervention will be assessed as the proportion of child contacts who are identified and whose families agrees for them to be screened by community-based clinic staff (community health worker, professional nurse, type of provider dependent on the setting) in their home. We will also summarize reasons for the refusal of a household visit in the intervention arm using proportions among those approached. Fidelity to guidelines will be summarized as the proportion of TB contacts initiated on the correct TPT regimen by age and HIV status, and the proportion of TPT initiations with the correct dose for weight to measure guideline fidelity of community-based TB preventive care.

Process outcomes to be reported will include drug shortages and stockouts, stockouts of supplies needed for pediatric specimen collection, stockouts of TB and contact file and registers, other materials needed for the intervention (scale, etc.), staffing within the TB clinic and community health teams, use of community health teams to do contact tracing in control clinics, changes in key personnel including community health workers and TB nurses, and time the TB nurse and/or community health worker is pulled away from TB activities.

All analyses will be conducted using STATA software (StataCorp. 2021) [25].

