### Limitations

Prior to study initiation, routine medical records in both South Africa and Ethiopia lacked sufficient detail to be able to collect the necessary data for all primary and secondary outcomes. Study-wide implementation of a child contact management form was needed across intervention and control clinics. Data points were pragmatic and consistent with best practices from the WHO TPT handbook [19]. Healthcare workers will be relied upon to collect these data. We will minimize missing and erroneous data by conducing pre-trial data collection training and by regularly performing data quality checks at each facility and reinforcing training for healthcare workers as needed.

Training of healthcare workers, reinforcement of data collection processes, and the presence of research staff may increase the quality of child contact management in standard of care facilities, which may therefore limit the effect size of the intervention.

In South Africa, research nurses will be hired to conduct the household visits due to overall staff and OTL shortages. This may impact the generalizability of the study results in South Africa. However, this will not be the case in Ethiopia where the health extension workers, employed by the health system, will be implementing the study.

We expect that between-cluster contamination will be limited by country guidelines that require TB patients to seek care at the clinic to which their home is assigned to ensure the clinic’s ability to provide directly-observed therapy for the TB index patient. This, however, is variably enforced by clinics in South Africa where anyone who lives within the catchment area of the study will be treated based on where the index patient sought care. This information will be collected and, if relevant, may be used in sensitivity analyses.

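### TPT completion has two conflicting definitions, doses taken and visits made, and the visit rule could favour home-based care if visits are kept more often at home

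*Protocol article*

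**What the plan says.** Table 1 of the protocol article (Objectives and endpoints) lists treatment completion as a secondary outcome and defines it by doses within a window: "Treatment completion was defined as 11 doses in 16 weeks for 3HP and 68 doses in 4 months for 3RH". It gives no rule for 6H, although Table 2 lists 6H for children on ART in both countries.

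The section Primary and secondary outcome analyses defines the same outcome by attendance: "TPT completion will be defined as three monthly follow-up visits over a 4-month period (3HP or 3HR"). I read 3HR there as 3RH. For the longer regimen the rule is again a visit count: "or six monthly visits over a 9-month period (6H"). No dose or pill-count condition is attached.

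That section also compares between arms "the proportions of these who are screened, initiated on TPT and who complete TPT", using cluster-level proportions and a t-test.

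On how follow-up is delivered, Treatment follow-up and adherence says: "Children initiated on TPT will be followed at home (intervention) or in clinic (control) monthly for the duration of TPT". It adds: "Adherence will be measured by return visits and pill counts in both groups". The Limitations section states: "In South Africa, research nurses will be hired to conduct the household visits due to overall staff and OTL shortages".

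**The concern.** Two rules for one outcome, with neither named as governing, leave the analyst to choose. The Study design section says that data analysts are not masked, so the choice should not be left until the data can be seen.

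The visit rule also measures something different in each arm. In the intervention arm a follow-up visit is something the health team brings to the household. In the control arm it generally means that the family comes to the clinic. A rule that counts visits and ignores intake may therefore partly record how follow-up was delivered rather than whether the course was taken. Completion is also the last step of the continuum-of-care outcome in Table 1, so the choice of rule carries through to that result.

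**Working it through.** The plan gives no figure to reproduce here. The check sets the two rules side by side and then asks what the visit rule does when dose-taking is held equal.

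**1. The rules compared**

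| | Table 1 | Analysis section |
|---|---|---|
| 3HP | 11 doses in 16 weeks | 3 monthly visits in 4 months |
| 3RH | 68 doses in 4 months | 3 monthly visits in 4 months |
| 6H | no rule | 6 monthly visits in 9 months |

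- 3HP is 12 weekly doses, so Table 1 asks for 11/12 = 91.7% of them. The visit rule asks for no minimum.
- For 3RH, if three months of daily treatment is taken as 84 to 90 doses (an assumption), Table 1 asks for 68/90 = 75.6% to 68/84 = 81.0%. Again the visit rule asks for no minimum.
- The 3HP windows also differ: 16 × 7 = 112 days against 4 × 30.4375 = 121.75, about 122 days.

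**2. Children classified differently**

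- A child on 3HP is seen three times in 4 months and takes 8 of 12 doses. This child is complete by visits and, since 8 < 11, not complete by doses.
- A child on 3HP takes 11 doses in 16 weeks and has two recorded visits. This child is complete by doses and not complete by visits.

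**3. Bias in the between-arm comparison**

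Let V be the proportion meeting the visit rule and D the proportion meeting the dose rule, in the intervention (I) and control (C) arms, on the same denominator. If the visit result is read as treatment completion, then

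bias = (V_I − V_C) − (D_I − D_C).

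The documents give neither V nor D, so all rates below are assumptions. With equal dose completion (D_I = D_C):

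| V_I v V_C | Bias | Ratio V_I/V_C |
|---|---|---|
| 90% v 90% | 0 points | 1.00 |
| 90% v 80% | 10 points | 1.12 |
| 95% v 70% | 25 points | 1.36 |

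With unequal dose completion the result can vanish or change sign. If doses are completed by 80% v 70%, visits of 90% v 80% give 10 − 10 = 0 points, and visits of 90% v 90% give 0 − 10 = −10 points, which is against the intervention.

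These rates are per child initiated. The analysis section also uses identified contacts as a denominator. The same formula applies there with all four proportions on that base, but the point values would differ.

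**4. Consequence for the planned test**

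A simulation used the planned unpaired t-test on cluster proportions (two-sided 5%) with 9 clinics per arm, as in Sample size considerations. It assumed an intracluster correlation of 0.05 and about 30 initiated children per intervention clinic and 15 per control clinic. With dose completion equal, the visit rule gave a significant result in about 5%, 42% and 99% of runs for the three rows of the table. These percentages depend entirely on the assumed inputs.

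**The case against.** The strongest reply is that visits are a reasonable operational proxy for treatment and that no direction of bias has been shown. Much of this stands.

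- **Visits are tied to drug supply.** Under Intervention arm, the Ethiopian health extension worker brings one month of medication at a time, and the follow-up section itself lists return visits as an adherence measure. Part of any difference in visits may be a real difference in treatment received.
- **Home visits are not guaranteed.** Table 1 tracks visit attempts per household and invalid addresses. Under Control arm, clinics may use community health workers to check on children who may have dropped out of care.
- **One supporting sentence is weak.** The statement that the team "will revisit the household monthly for three months to ensure linkage to care" directly follows the referral of symptomatic children. It does not clearly describe TPT follow-up.
- **Pill counts have limits too.** A count would ordinarily need a visit, so a child who stops attending may lack one, and more often in one arm.

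A reader might therefore infer that the visit rule favours the intervention whatever the child takes, or that any gap in visits is wholly spurious. The documents do not support either reading: they give no visit-keeping rates, and the bias is zero when the visit and dose differences match. The rule does ignore intake, but that does not make real intake the same in both arms.

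The reply does not remove the contradiction. The article never calls the visit rule a proxy for the dose rule. It states each as the definition.

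**Conclusion.** The contradiction is plain in the text: a dose rule for two regimens in Table 1, and a visit rule for three in the analysis section, with no statement of which applies. It is a conflict between two stated rules, not detail left to another document.

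The bias is conditional. The visit rule could favour the intervention if visits are kept more often at home than in clinic without a matching difference in doses taken. The size is unknown. The 0, 10 and 25 points above rest on assumed visit rates and on equal dose completion. Direction is a reasonable expectation from where follow-up takes place, not something the documents establish.

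The effect is confined to completion and the outcomes built on it. The primary outcome, TPT initiation, is unaffected.

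**What to change.** 1. Reconcile Table 1 and the analysis section to a single definition covering every regimen used, including 6H, with dose thresholds and windows confirmed by the sponsor. This review takes no position on which threshold or window is right.
2. Base the between-arm comparison on medication intake from the pill counts planned in both arms. Confirm that they are abstracted, because the extraction list under Outcome data does not name them.
3. Report missing pill counts by arm, with a sensitivity analysis, for example one counting children without a final count as non-completers and one restricted to children with a count.
4. Report visits kept as a separate process measure, by arm.
5. Loss to follow-up can stay visit-based, with a note that it shares the home-versus-clinic asymmetry.

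Suggested wording, with the bracketed items for the sponsor to fill: *A child has completed TPT if pill counts show at least [number] doses of the assigned regimen taken within [window], specified separately for 3HP, 3RH and 6H. The same rule applies in both arms. Visits kept are summarised separately and do not define completion.*

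The cost is a wording change plus some added abstraction if pill counts are not already extracted. The downside is missing pill counts, possibly more in one arm, which is why item 3 is needed. The change should be settled before the outcome data are compared by arm.

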## Methods

### Study design

This is a pragmatic, parallel, cluster-randomized, controlled, superiority trial comparing a home-based versus a facility-based care delivery model for contact management. Clinics were randomized in a 1:1 ratio to conduct either home-based (intervention) or facility-based (standard of care) contact management. Randomization was stratified by country, local geography, and TB notifications. Given that the intervention is carried out by a clinic in its entirety, neither the patient, provider/outcome assessor nor the study team including data analysts will be masked to the study procedure.

Routine program data will be collected by healthcare workers and abstracted by the study team retrospectively. Prior to trial implementation, a standardized child contact management form will be implemented in both settings to standardize data collection by all facilities in both arms. The tool was adapted from a previous trial by each country team and in conjunction with the parent IMPAACT4TB project [6, 20, 21]. Children will be evaluated monthly until they complete TPT, as per the Ethiopian and South African National Guidelines. Concomitant interviews will not be prohibited.

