### Data collection

#### Outcome data

Clinical outcome data will be extracted from patient records maintained by the community health teams and the clinic. Outcome variables that will be retrospectively extracted from the child contact file include presence of symptoms (binary, yes/no will be asked for each symptom), gastric aspirate/Xpert/culture results (if applicable), chest X-ray results (if applicable), the TPT or active TB treatment initiation date, the TPT regimen, planned and actual dates of all follow-up visits, TPT completion date, and reasons for early discontinuation including patient preference, pregnancy (adolescents), and severe disease including malaria or side effects including flu-like illness, hypersensitivity reactions, hepatotoxicity, and peripheral neuropathy (if applicable). We will collect information regarding the location of child contact screening, TPT initiation, and all subsequent follow-up visits. We recognize these outcomes are dependent on clinic staff compliance with study tools. Periodic monitoring of study tools will be performed, and additional training will be provided if study tools are not being used optimally.

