### Data management

A child contact management record will be implemented and maintained by healthcare workers. The child contact management record will be maintained at the health facility in both the intervention and control clinics. Additionally, in Ethiopia, health extension workers will maintain a record in the community at the health post (intervention arm only). These data will be synced with the clinic file monthly. Data will be extracted retrospectively from these routine clinic charts either onto clinical research forms (Ethiopia) or directly into a REDCap database (South Africa), no less than one month after the clinic visit to allow sufficient time for charting.

Data will be entered and maintained on a secure, password-protected, web-based REDCap database with multisite access with secure web authentication and secure sockets layer encryption. The data constitutes a limited data set and does not include identifiers like name, date of birth, address or phone number, medical record number, and identity number.

This small, unmasked study presents minimal risk to study participants and therefore does not meet criteria for a data safety and monitoring board.

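### Incident TB after TPT start is sought at visits whose place is the randomised intervention and is abstracted from the contact files, so the by-arm comparison is open to differential detection of unknown direction and size

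*Protocol article*

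**What the plan says.** Table 1 of the Protocol article (Objectives and endpoints) lists incident TB, labelled treatment failure, as a proportion of children initiated on TPT. It is one of several categories under treatment completion, and loss to follow-up is another.

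The way it is found is set out in four places:

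- **Study design:** "Children will be evaluated monthly until they complete TPT". Neither providers, outcome assessors nor analysts are masked.
- **Treatment follow-up and adherence:** "Children initiated on TPT will be followed at home (intervention) or in clinic (control) monthly for the duration of TPT", and "Children will also be re-screened for TB symptoms during each follow-up visit".
- **Outcome data:** "Clinical outcome data will be extracted from patient records maintained by the community health teams and the clinic". The variables to be taken retrospectively from the child contact file include "the TPT or active TB treatment initiation date".
- **Primary and secondary outcome analyses:** "All data will be abstracted by study staff from index patient and child contact management files". Loss to follow-up means no return visit within three months of the last recorded visit. Outcomes are summarised by arm and tested formally if there are enough events.

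Data management adds a health-post record kept by health extension workers in Ethiopia's intervention arm only, synced monthly with the clinic file. Interim analysis says treatment failures will be monitored, and gives as the purpose the safety of children cared for by health extension workers in that same arm.

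**The concern.** The opportunity to detect TB is a follow-up visit, and the place of that visit is what was randomised. If the two arms keep different proportions of children in follow-up, or reach a confirmed diagnosis by different routes, recorded incident TB can differ with no difference in true risk.

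The handling of lost children adds to this. A child who started TPT and then stops attending remains in the denominator. TB after the last visit counts only if it finds its way into the contact file. The article describes no common check of TB status for all initiators and does not name the TB treatment register as a source.

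At stake is the reading of a by-arm safety summary. There is no data safety and monitoring board and there are no stopping guidelines, so completeness of this count matters more than its secondary status suggests.

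**Working it through.** The article gives no figure for this outcome to reproduce: no TB risk, attendance or detection probability by arm. The check is therefore a comparison of the stated procedures, followed by an illustration on assumed inputs.

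**1. What is the same and what differs by arm**

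- Same: the national screening tool (TB screening and evaluation), the monthly schedule and re-screening at each visit.
- Different: the place of the visit. In the intervention arm the team goes to the household. In the control arm the family returns to the clinic, and community health workers may, but need not, assess children at risk of being lost (Control arm).
- Different: the additional health-post record in Ethiopia's intervention arm.
- Possibly different: the route to confirmation. At the initial home visit a symptomatic child is referred to the clinic (Intervention arm). If the same applies at follow-up, home care has one more step at which a case can be lost.

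**2. Effect of unequal detection**

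Let p be the true risk, equal in both arms, and d the probability that a case is recorded. Observed risk = p × d, so the observed ratio (home to clinic) = d(home) / d(clinic), and p cancels.

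| Assumed d, home | Assumed d, clinic | Observed ratio |
|---|---|---|
| 90% | 90% | 1.00 |
| 90% | 60% | 0.90/0.60 = 1.50 |
| 80% | 70% | 0.80/0.70 = 1.14 |
| 80% | 90% | 0.80/0.90 = 0.89 |

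**3. Partial detection before loss**

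If d is read as retention, the second row assumes that no case is found in a child who is later lost. Suppose instead that half of the cases in lost children are recorded (an assumption). With retention of 90% and 60%, d(home) = 0.90 + 0.10 × 0.5 = 0.95 and d(clinic) = 0.60 + 0.40 × 0.5 = 0.80. The ratio is 0.95/0.80 = 1.19, so 1.5 is towards the upper end for that retention gap.

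**4. How many events to expect**

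Initiators per arm = 9 clinics × index patients per clinic × initiations per index patient, from Sample size considerations.

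- South Africa: 9 × 40 × 0.5 = 180 control; 9 × 40 × 1.0 = 360 intervention.
- Ethiopia: 9 × 26 × 0.6 = 140.4 control; 9 × 26 × 1.2 = 280.8 intervention.
- Total: about 320 and 641. The South African rates start from children under 15, while enrolment there is under 5, so these totals may be high.

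True cases, control versus intervention: 1.6 and 3.2 at an assumed risk of 0.5%; 3.2 and 6.4 at 1%; 6.4 and 12.8 at 2%. At 2%, with detection of 60% in clinic and 90% at home, 3.8 and 11.5 cases would be recorded.

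For that last case the 95% interval on the ratio of 1.5, ignoring clustering, follows from SE(log ratio) = √(1/3.8 + 1/11.5 − 1/320 − 1/641) ≈ 0.59. The limits are 1.5 × exp(±1.96 × 0.59), about 0.5 to 4.7.

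**The case against.** The best defence has four parts, and much of it stands.

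- **Sources are wider than one sentence suggests.** The Outcome data section names records of the community teams and the clinic, and the TB treatment start date is a planned variable in both arms. A reader might infer that TB in a child who stopped attending cannot be recorded. The article does not say that, nor that a file is closed at loss to follow-up. What remains is that this section, like the analysis section, takes the variables from the contact file, and no other source is named for later TB.
- **Direction.** A reader might infer that home visits find more TB. Nothing in the document states it, the nominal procedures are equal, and an extra referral step could work the other way.
- **Length of observation.** Ending at TPT completion fits an outcome labelled treatment failure and is not an error in itself. Regimens differ in duration, but they follow country, age and rifamycin contraindication rather than arm, so this is no built-in arm bias. Referred symptomatic children who never start TPT fall outside the outcome by definition; the plan has household revisits for linkage and a continuum-of-care outcome.
- **Weight.** The outcome is secondary, events would be few, and random error would be larger than the illustrated bias. This argues for a modest correction. With so few events, though, a handful missed in one arm could alter the picture.

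**Conclusion.** The point holds in limited form. Ascertainment of incident TB depends on arm-specific visits and routine contact files, is unmasked, and leaves children lost to follow-up in the denominator with TB status possibly unknown. The by-arm comparison is therefore open to differential detection, and the documents settle neither its direction nor its size.

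The ratios of 1.5, 1.14 and 0.89 show what is possible under assumed detection probabilities and equal true risk; they are not estimates for this trial. It would go too far to call the comparison uninterpretable or incident TB the trial's main harm outcome, since the article lists it as one treatment-outcome category among several. The primary outcome, TPT initiation per index patient, is not touched. The change is worth making because it is inexpensive and the count also serves as the stated safety monitoring.

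**What to change.** In Primary and secondary outcome analyses:

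- Add the study clinic's TB treatment register as a source for incident TB.
- Have the abstractors check every enrolled child who started TPT, including those lost to follow-up, against that register. Do this at one fixed time after TPT start that is the same in both arms and falls within the planned data-abstraction period.
- Do the check on site before de-identified entry, because the database holds no names or record numbers.
- Report incident TB by arm with all initiators as the denominator, beside the proportion with known TB status by arm, and treat the comparison as descriptive.
- For enrolled children who screen symptomatic (in the intervention arm, those referred from the home), report by arm how many were evaluated and how many started TB treatment, from data already collected.

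The cost is a small amount of extra abstraction at the 36 clinics by staff already working from their records. TB treated at other facilities would still be missed. Checking contacts without consent, or extending follow-up of every child, would not be clearly cheap and is not needed for this point.
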